#### Co-interventions

If participants experience unbearable pain during menstruation, taking NSAIDs is permitted. The participants will be asked to record whether they take the NSAIDs or not. Other drugs that alleviate menstrual pain or acne- such as topical or systemic corticosteroids, herbal medicine, oral contraceptives, topical or oral vitamin A derivatives and antibiotics- are prohibited.

### Outcomes

The detailed outcome measurement time points are provided in Table 1.

**Table 1 Tab1:** Study process treatment and outcome measurements

Activity	Visit 1	Visit 2	Visit 3	Visit 4	Visit 5	Visit 6	Visit 7	Visit 8
Time Schedule	Week 1	Baseline	Week 2	Week 4	Week 6	Week 8	Week 12	Week 16
Window visit		±3 days	±3 days	±3 days	±3 days	±3 days	±3 days	±3 days
Demographic information-taking	X							
Informed consent form	X							
General medical history-taking	X							
Photographing the patient’s face Count of inflammatory/non-inflammatory lesions	X	X	X	X	X	X		
Blood tests (liver function test, renal function test)	X					X		
Blood tests		X				X		
Urine pregnancy test	X					X		
Randomization & allocation		X						
Investigational Produce		X	X	X	X			
Numeric rating scale (menstrual pain)		X		X		X	X	X
Verbal multidemensional scoring system grade	X	X		X		X	X	X
Investigator’s Static Global Assessment Scale of Facial Acne Vulgaris		X	X	X	X	X		
Numeric rating scale (acne)		X	X	X	X	X	X	X
Monitoring adverse events			X	X	X	X	X	X
Compliance check			X	X	X	X		
Blinding check						X		

#### Primary outcomes

Primary outcome will be presented as the mean percentage change in total lesion counts from baseline to the end of the treatment. Total lesion counts refer to the sum of the inflammatory and non-inflammatory lesions. Inflammatory lesions included inflammatory papules, pustules, and cysts and non-inflammatory lesions include black and white head comedones. The front and both sides of each participant’s face will be photographed on each visit using a Lumix-LX2 digital camera (Panasonic, Osaka, Japan). Two Korean medicine doctors who have been in clinical practice for more than 3 years will count the lesions independently. Discrepancies will be resolved by discussion with a third researcher.

#### Secondary outcomes

Secondary outcomes will be assessed using the numeric rating scale (NRS) for dysmenorrhea and acne vulgaris, VMSS for dysmenorrhea, investigator’s static global assessment scale of facial acne vulgaris, and laboratory tests.

##### Dysmenorrhea

The NRS and VMSS for dysmenorrhea will be evaluated at baseline, 4 weeks, 8 weeks, f/u 4 weeks, and f/u 8 weeks. The mean difference in NRS and VMSS between herbal medication treatment and placebo group will be assessed at 8 weeks. The difference in NRS and VMSS between two groups will also be assessed according to time points.

##### Acne vulgaris

The mean percentage change in inflammatory and non-inflammatory lesion counts from baseline to the end of treatment (8 weeks) will be evaluated as secondary outcomes. We will also analyze the mean difference in NRS and investigator’s static global assessment scale of facial acne vulgaris between herbal medication treatment and placebo group at 8 weeks. Furthermore, the difference in NRS and investigator’s static global assessment scale of facial acne vulgaris between two groups will be assessed every 2 weeks (0–8 weeks).

### Safety and adverse event outcomes

#### Safety

Safety will be investigated using adverse reaction reports and clinical laboratory tests. We will examine blood test results (BUN, creatinine, ALT, AST) and urine hCG levels at screening (visit 1) and 8 weeks (visit 6).

#### Adverse events

We will evaluate and classify the adverse events (AEs) at every visit throughout the trial. An AE is an undesirable, unintended sign, symptom, or disease that does not necessarily have a cause–effect relationship with the intervention evaluated in a clinical trial. We will continuously monitor AEs and make any decision in this regard on the basis of both objective and subjective signs as well as blood test results. Appropriate measures will be taken immediately to minimize any SAEs.

### Sample size calculation

We referred to similar studies that investigated the effects of herbal medicine for dysmenorrhea [17, 21]. The mean difference for the treatment group and placebo group was assumed to be 2.21 and 1.28, respectively. Pooled SD was assumed to be 2.24 based on the same studies. We set α at 0.05 and 1-β at 0.8 and calculated the necessary sample size. Assuming a 15% dropout rate and an allocation ratio of 1, the sample size was calculated to be 116 (58 participants in each group).

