**Methods:**

This is a protocol for a randomized, double-blind, parallel-group, placebo-controlled and multicenter trial. One hundred and sixteen participants with dysmenorrhea accompanied by acne vulgaris will be recruited at three centers and randomized into two groups, the herbal treatment group and placebo group. The participants will receive GBH or DJS based on pattern identification or placebo granules thrice daily for 8 weeks, with an 8-week follow up. The primary outcome will be the mean percentage change in the count of inflammatory acne lesions. The secondary outcomes would be based on dysmenorrhea numeric rating scale, verbal multidimensional scoring system for dysmenorrhea, acne numeric rating scale, investigator’s static global assessment scale of facial acne vulgaris, and safety testing. Adverse events will also be reported.

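### The sample size rests on a dysmenorrhea effect, so 80% power is not shown for the acne primary outcome; nor do the stated inputs give 116.

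*Protocol article*

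**What the plan says.** The Sample size calculation section of the protocol article gives a complete set of inputs:

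- Source: "We referred to similar studies that investigated the effects of herbal medicine for dysmenorrhea".
- Effect: "The mean difference for the treatment group and placebo group was assumed to be 2.21 and 1.28, respectively". No scale or unit is named.
- SD: "Pooled SD was assumed to be 2.24 based on the same studies".
- Error rates: "We set α at 0.05 and 1-β at 0.8 and calculated the necessary sample size". One- or two-sided is not stated.
- Result: "Assuming a 15% dropout rate and an allocation ratio of 1, the sample size was calculated to be 116 (58 participants in each group").

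The outcome under test is a different one. Under Primary outcomes: "Primary outcome will be presented as the mean percentage change in total lesion counts from baseline to the end of the treatment". The Methods part of the Abstract names inflammatory lesions instead: "The primary outcome will be the mean percentage change in the count of inflammatory acne lesions". Both are acne counts. The dysmenorrhea scales are placed lower: "Secondary outcomes will be assessed using the numeric rating scale (NRS) for dysmenorrhea and acne vulgaris, VMSS for dysmenorrhea".

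The Primary endpoint section plans an independent t-test or Mann-Whitney test on percentage change in total lesion count. It sets the significance level at 0.1, not the 0.05 used for the sample size.

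**The concern.** Power belongs to one test on one variable. The calculation takes its effect and SD from studies of one condition, and the trial tests its primary hypothesis on another. Percentage change in a lesion count has its own spread and its own plausible effect, and the article gives neither. It also offers no argument that the dysmenorrhea effect can stand in for an effect on acne. Whether treating the first condition also improves the second is the question that the trial asks, so an equal standardised effect cannot be taken for granted.

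A reader will nevertheless take the 80% as describing the acne comparison, on which superiority is to be declared. If that comparison is not significant, the article gives no help in judging how large a lesion-count effect the trial could have been expected to find.

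The arithmetic raises a second question: whether 116 gives 80% power even for the effect that was used.

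**Working it through.** **Inputs.** From Sample size calculation: means 2.21 and 1.28, SD 2.24, alpha 0.05, power 0.80, dropout 15%, 58 per arm. From Primary endpoint: alpha 0.1. From Intent-to-treat population: everyone who took at least one dose is included, with last observation carried forward (LOCF).

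**Step 1. Standardised planning effect.** 2.21 − 1.28 = 0.93, and 0.93 / 2.24 = 0.415.

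**Step 2. Can 116 be reproduced?** The normal approximation is n per arm = 2 × (z_alpha + z_power)² / 0.415². At two-sided 0.05 this is 2 × (1.960 + 0.842)² / 0.415² = 91.1, so 92. The noncentral t gives 92.04, so 93. Allowing for dropout, 92 / 0.85 = 108.2, so 109 per arm and 218 in total; 93 / 0.85 = 109.4, so 110 per arm and 220 in total.

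Because sidedness is not stated and a second alpha appears, the other readings were tried (normal approximation):

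| Reading of alpha | n per arm | Total with 15% dropout |
|---|---|---|
| Two-sided 0.05 | 92 | 218 |
| One-sided 0.05 (same as two-sided 0.10) | 72 | 170 |
| One-sided 0.10 | 53 | 126 |

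None gives 116. A one-sample t formula gives 48, then 48 / 0.85 = 56.5, so 57 per arm and 114 in total. That is close, but it does not fit a comparison of two groups, so it is at most a possible explanation.

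**Step 3. Power of 116 for the planning effect.** 58 × 0.85 = 49.3, so about 49 per arm are evaluable. Noncentral t, effect 0.415, two-sided:

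| n per arm | Alpha 0.05 | Alpha 0.10 |
|---|---|---|
| 49 | 53% | 65% |
| 58 | 60% | 72% |

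**Step 4. What 116 can detect on the primary outcome.** No lesion-count effect or SD is given, so neither power nor a corrected N can be computed. The detectable difference in SD units can be. Noncentral t, 80% power, two-sided:

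| n per arm | Alpha 0.05 | Alpha 0.10 |
|---|---|---|
| 49 (evaluable after dropout) | 0.572 | 0.506 |
| 58 (all randomised, LOCF) | 0.525 | 0.464 |

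All four values exceed the planning effect of 0.415.

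**Step 5. In percentage points.** The SDs below are assumptions for illustration and do not come from the article. With 49 per arm, difference = standardised value × SD:

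| Assumed SD of percentage change | Alpha 0.05 (0.572 × SD) | Alpha 0.10 (0.506 × SD) |
|---|---|---|
| 30 | 17.2 | 15.2 |
| 40 | 22.9 | 20.2 |
| 50 | 28.6 | 25.3 |
| 60 | 34.3 | 30.4 |

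**The case against.** The Background says that no study has yet examined whether herbal treatment of dysmenorrhea improves acne related to the menstrual cycle. The planners may therefore have had no acne figure for these medicines, and a neighbouring literature is an understandable source. That explains the choice of inputs. It does not make the resulting power a property of the acne test.

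It can also be said that a journal article condenses a longer document. Here, though, the calculation is given in full, and the difficulty lies in what it states.

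Three stronger readings are tempting, and the article supports none of them:

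- **The trial is underpowered for acne.** This is not shown. Power is unknown, and with 49 per arm at two-sided 0.05 it would exceed 80% if the true standardised effect were above about 0.57. That a smaller effect would be missed more often is true of any trial of this size.
- **A non-significant result could not be interpreted.** This goes too far. A confidence interval for the lesion-count difference can be read whatever the planning basis.
- **The 80% is at least right for dysmenorrhea.** Steps 2 and 3 show otherwise.

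Two cautions about the figures stand. First, 49 per arm is a conservative planning number. The main analysis is intention-to-treat with LOCF, so up to 58 per arm may enter the test, although carried-forward values add no real information. Second, the source of 2.21, 1.28 and 2.24 is explicit but their scale is not. That they are pain scores is an inference.

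**Conclusion.** The point holds in two parts.

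First, the stated 80% power comes from a dysmenorrhea effect and is not shown for the primary analysis. This is so whether the primary outcome is the total or the inflammatory lesion count. It rests on the text alone and needs no assumption.

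Second, the stated inputs do not give 116. At two-sided 0.05 they call for roughly 1.9 times as many participants (218 / 116 = 1.88). No other reading of alpha that was tried brings the total below 126. This part assumes a two-group comparison of means with the stated SD.

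For the primary outcome, 116 participants give 80% power for a standardised difference between 0.46 and 0.57, depending on n and alpha. These values assume a t-test; if the Mann-Whitney alternative is used they are approximate. The percentage-point figures depend wholly on the assumed SDs and illustrate the range only.

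**What to change.** Keep 116 and rewrite the sample size paragraph so that it:

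1. says that the planning means and SD came from dysmenorrhea studies, and names their scale;
2. removes the 80% power claim for both the acne and the dysmenorrhea effect;
3. uses one alpha, with sidedness stated, in both Sample size calculation (now 0.05) and Primary endpoint (now 0.1);
4. states the detectable difference for the primary outcome with its n and alpha.

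Suggested wording for item 4, keeping one value from each bracket:

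> With 49 evaluable participants per arm, the trial has 80% power at two-sided alpha [0.05 / 0.10] to detect a between-group difference of [0.57 / 0.51] SD in percentage change in total lesion count.

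If the intention-to-treat set of 58 per arm is to be described instead, the values are 0.525 and 0.464. A short table over plausible SDs should follow, labelled as assumed unless a source is cited. An 80% claim for the acne outcome should return only if a lesion-count difference and SD are supplied that support it.

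The cost is one paragraph and a decision on alpha. No participants are added. The drawback is that the stated power becomes less favourable.

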#### Primary endpoint

An independent t-test (or Mann-Whitney U test) will be used to compare the mean percentage change in total lesion counts from baseline to the end of the treatment between the two groups in terms of the primary outcome. Superiority will be confirmed when there are statistically significant differences. The level of significance will be set at a *P* value of 0.1.

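### The stated sample-size inputs do not give 116; that figure follows only if 1.28 is the between-group difference rather than the placebo-arm value

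*Protocol article*

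**What the plan says.** The Sample size calculation section of the protocol article takes its inputs from earlier studies of herbal medicine for dysmenorrhea and gives a complete set:

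- Effect: "The mean difference for the treatment group and placebo group was assumed to be 2.21 and 1.28, respectively".
- Variability: "Pooled SD was assumed to be 2.24 based on the same studies".
- Error rates: "We set α at 0.05 and 1-β at 0.8 and calculated the necessary sample size". The section does not say whether alpha is one-sided or two-sided.
- Attrition and allocation: "Assuming a 15% dropout rate and an allocation ratio of 1".
- Result: "the sample size was calculated to be 116 (58 participants in each group").

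The planned primary analysis, under Primary endpoint, is a two-group comparison: "An independent t-test (or Mann-Whitney U test) will be used to compare the mean percentage change in total lesion counts". The same section adds: "The level of significance will be set at a *P* value of 0.1".

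**The concern.** The sentence on the effect attaches one number to each arm, so the difference to be detected is 2.21 − 1.28 = 0.93. Against an SD of 2.24 this is a standardised difference of 0.93/2.24 = 0.415, and 58 per group before dropout looks too few for 80% power at that size of effect.

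This section is the only justification given for recruiting 116 women. If its inputs and its result disagree, a reader cannot tell what difference the trial was sized to detect, or whether the 80% describes the trial's own assumptions. The gap is not one that a fuller document could fill by adding detail, because the inputs and the result are all printed and conflict with each other.

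**Working it through.** **Inputs** (all from Sample size calculation): arm values 2.21 and 1.28; SD 2.24; alpha 0.05; power 0.80; dropout 15%; allocation 1:1. Two-sided testing is an assumption, and the one-sided case is also shown.

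**Formula.** Evaluable number per group for two means, normal approximation: n = 2 × [(z_alpha + z_power) × SD / difference]². The number randomised per group is n / (1 − 0.15).

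**Step 1: reproducing 116.** With 1.28 as the between-group difference and two-sided 0.05:

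- n = 2 × [(1.960 + 0.842) × 2.24 / 1.28]² = 48.07, so 49.
- 49 / 0.85 = 57.6, so 58 per group and 116 in total.

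The match is exact, with every other input as stated. (Solving with the t distribution gives 49.05 instead of 48.07; strict rounding up then gives 50, hence 59 per group. The match is therefore to the usual normal-approximation formula.)

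**Step 2: the inputs as written.** With difference 0.93 and two-sided 0.05:

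- n = 2 × [(1.960 + 0.842) × 2.24 / 0.93]² = 91.07, so 92 (t-based 92.04, so 93).
- 92 / 0.85 = 108.2, so 109 per group and 218 in total (220 on the t basis).

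**Step 3: can another convention rescue 116 with difference 0.93?**

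| Alpha | Evaluable per group | Randomised per group, n/0.85 | Total | Per group if inflated as n × 1.15 |
|---|---|---|---|---|
| two-sided 0.05 | 92 | 109 | 218 | 106 |
| one-sided 0.05 (same as two-sided 0.1) | 72 | 85 | 170 | 83 |
| one-sided 0.10 | 53 | 63 | 126 | 61 |

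None gives 58 per group. Nor does taking 2.21 as the difference: that needs 17 evaluable and 20 randomised per group. To keep difference 0.93 with 49 evaluable per group at two-sided 0.05 and 80% power, the SD would have to be 0.93 / [2.802 × √(2/49)] = 1.64, not 2.24.

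**Step 4: power on the literal reading** (difference 0.93, SD 2.24, two-sided 0.05). The normal approximation is Φ(0.93 / [2.24 × √(2/n)] − 1.960):

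- n = 49 (58 × 0.85 = 49.3): Φ(2.055 − 1.960) = 0.538; noncentral t 0.530.
- n = 58 (everyone analysed): Φ(2.236 − 1.960) = 0.609; noncentral t 0.601.

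**Step 5: power if 1.28 is the difference** (same alpha, normal approximation): 0.807 with 49 per group and 0.868 with 58. The stated 80% then holds.

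**The case against.** The strongest reply is that only the sentence is wrong. A difference of 1.28 returns 116 exactly with every other input unchanged, which suggests a coherent calculation described badly. In that case the trial has its stated 80% power and nothing but the wording needs repair. This stands as a real possibility. The source studies are not available here, so it cannot be confirmed or excluded. It does not remove the conflict, since the paragraph as printed is still wrong.

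A reader might go further the other way and infer that the trial is underpowered, with 58 per group giving only about 53% power. The document does not support that, for three reasons:

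- 53% belongs to 49 evaluable per group. With 58 analysed it is about 60%, and the Intent-to-treat population section includes everyone who took at least one dose and fills gaps by carrying the last observation forward, so the number analysed may be close to 58.
- Both figures hold only if 2.21 and 1.28 really are the arm values.
- Both assume a two-sided test, which the section does not state.

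It is also fair to say that none of these percentages is the power of the primary comparison. The effect size comes from dysmenorrhea studies, while the primary outcome is percentage change in total lesion count. For the same reason, running this effect size at the 0.1 level set under Primary endpoint would not give the power of that test. The point is therefore limited to the internal consistency of the paragraph.

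**Conclusion.** The point holds as a contradiction between the stated inputs and the stated result. As written, the inputs require about 218 participants at two-sided 0.05, or 170 at one-sided 0.05, against the stated 116. No combination tried of alpha, sidedness or dropout inflation with a difference of 0.93 gives 58 per group, while a difference of 1.28 gives it exactly.

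On the literal reading the stated 80% becomes about 53% (49 evaluable per group) or about 60% (58 analysed per group) at two-sided 0.05. If 1.28 was the intended difference, 80% is right and the sentence is wrong. Confidence is high that text and figure do not reconcile; which of the two is at fault is undetermined. The paragraph must be corrected because it is the trial's only stated basis for its size.

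**What to change.** Check the sample-size worksheet against the source studies, then rewrite the paragraph in one of two ways:

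- **If 1.28 was the intended between-group difference:** say so (difference 1.28, SD 2.24, 49 evaluable per group, 58 after 15% dropout), and keep 116 with 80% power at 49 evaluable per group.
- **If 2.21 and 1.28 are the arm values:** keep 116 and replace the 80% claim with about 53% (49 evaluable per group) and about 60% (58 analysed per group) at two-sided 0.05.

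In either case, state whether alpha is one-sided or two-sided, and state that the power refers to the effect size taken from the dysmenorrhea studies and not to the lesion-count primary outcome.

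The cost is one corrected paragraph and a look at the worksheet. The stated power may become less favourable. No extra enrolment is proposed.

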### Data management

Data entry and management will be completed by an independent data administrator to ensure data accuracy. All procedures comply with confidentiality standards for medical data. All data will be entered electronic case report form and all source document will be kept at the study site. Important protocol modifications during this study will be communicated to the Institutional Review Board, trial registry, investigators, trial participants and the journal of publication.

### Statistical analysis

We will analyze the data using the intent-to-treat (ITT) principle and per protocol principle. We, along with a professional statistician, will perform data analysis of the results. We will not perform the interim analysis.

#### Patient groups for data analysis

##### Intent-to-treat population

The ITT population will include all participants treated with at least one dose of the study drug. If the patients dropped out during the trial or if there is missing data, the “last observation carried forward” principle will be used to compensate for that data.

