## Background

Acne is a chronic inflammatory skin disease of the pilosebaceous unit. The primary causes of acne include increased sebum secretion, follicular hyperkeratinization, *Propionibacterium acnes* within the follicle, and inflammatory responses [1]. Acne is considered an adolescent affection, but over the last few years, adult acne have been increased [2–4]. Postadolescent acne appears to occur more frequently in women than in men [5, 6]. The unique features of adult acne in women are that it is related to the menstrual cycle [3, 7]. Up to 78% of women with acne have premenstrual flares [3]. Accumulation of sebum within the sebaceous glands due to changes in sex hormone secretion during ovulation and menstruation has been proposed as a potential contributor to premenstrual acne [8, 9]; however, the mechanism underlying this phenomenon remains unknown.

Because adult acne in women is associated with menstrual-related hormones, it is usually accompanied by menstrual abnormalities, i.e. dysmenorrhea. Primary dysmenorrhea is defined as pain during menstruation in the absence of pelvic problems [10–12]. The prevalence of dysmenorrhea varies from 16 to 83% in women of reproductive age [10, 13]. Oral contraceptives are used to treat dysmenorrhea [11] and administered to female patients with acne who do not respond to medication and are suspected of having hormonal abnormalities [14, 15]. But the actual frequency of prescribing oral contraceptives is low because of possible side effects such as nausea, vomiting, and weight gain and social conventions against single female patients consuming oral contraceptives.

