##### Per-protocol population

The per-protocol population will include patients who would consume more than 80% of the prescribed doses of the study drug and complete the trial.

Effectiveness will be evaluated by ITT principle and per-protocol principle. When analysis results are different, the ITT principle will be considered for the main analysis and subordinately, we will compare the results of the analysis based on the per-protocol principle. Demographic and safety test will be analyzed by ITT principle and the data for safety test will be used without adjustment.

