#### Secondary endpoint

An independent t-test (or Mann-Whitney U test) will be used for continuous variables and Chi-square test (or Fisher’s exact test) for categorical variables between groups. Group effect, time effect, and group × time effect for repeat measurement data will be analyzed by repeated-measures analysis of variance (ANOVA) or repeated-measures analysis of covariance (ANCOVA).

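### Last observation carried forward is the only handling of missing data in the main analysis, although lesion counts are expected to change over the 8 weeks, so the week-8 contrast can be biased in either direction

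*Protocol article*

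**What the plan says.** The section on the ITT population defines that set as everyone who took at least one dose and then fixes the handling of gaps: "If the patients dropped out during the trial or if there is missing data, the “last observation carried forward” principle will be used". The section on the per-protocol population says that when results differ, "the ITT principle will be considered for the main analysis and subordinately, we will compare the results of the analysis based on the per-protocol principle". The per-protocol set holds women who "consume more than 80% of the prescribed doses of the study drug and complete the trial".

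The primary outcome (Primary outcomes) is the "mean percentage change in total lesion counts from baseline to the end of the treatment". The test (Primary endpoint) is one comparison per woman: "An independent t-test (or Mann-Whitney U test) will be used to compare the mean percentage change in total lesion counts". Table 1 schedules the row "Count of inflammatory/non-inflammatory lesions" at screening, baseline and weeks 2, 4, 6 and 8. Repeated secondary measures (Secondary endpoint) "will be analyzed by repeated-measures analysis of variance (ANOVA) or repeated-measures analysis of covariance (ANCOVA".

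The Rejection and withdrawal criteria list, among others, use of prohibited drugs (including antibiotics and vitamin A derivatives), skin rash, flare or itching, gastrointestinal symptoms after taking the drug, and intake below 80% of doses. The sample size section assumes 15% dropout.

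**The concern.** Carrying the last count forward assumes that a woman's lesions would have stayed at that count until week 8. The trial exists to test whether counts change over those weeks, so the plan's own hypothesis speaks against the assumption. Because one dose is enough to enter the ITT set, a woman who leaves before week 2 can be scored as 0% change.

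The harm depends on who leaves and when. Gastrointestinal intolerance could remove more women from the active arm. A woman who turns to a prohibited acne drug because her skin worsens could keep an earlier, better count. Both routes are plausible under the listed criteria, and neither is certain.

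At stake is the main efficacy result. The plan names no analysis that would show how far it rests on the carried values: the per-protocol set drops non-completers altogether.

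**Working it through.** The plan gives no figure for the effect of missing data, so there is none to reproduce. What follows is an illustration.

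**Inputs from the protocol article**
- 58 women per arm and 15% dropout (Sample size calculation).
- Lesion counts at baseline and weeks 2, 4, 6 and 8 (Table 1), so a carried value comes from week 0, 2, 4 or 6.

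**Assumptions, not in the document**
- The mean fall in count is linear and reaches *m* percent at week 8.
- Women who leave would have followed the same course as the others in their arm.
- Within a scenario, all who leave have the same last visit, week *w*.
- True improvement is 40% (herbal) vs 20% (placebo), or 30% in both arms for no effect.
- The unequal split is 25% herbal vs 5% placebo. With equal arms this averages (25 + 5)/2 = 15%.

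**Exposure.** 0.15 × 58 = 8.7 per arm, so about 17 of the 116 primary values would be carried forward.

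**Formula.** With dropout proportion *p*, the expected arm mean is (1 − p)·m + p·m·(w/8) = m·[1 − p·(1 − w/8)].

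**Contrast, herbal minus placebo improvement, in percentage points**
- True difference 20, dropout 15%/15%: 20·[1 − 0.15·(1 − w/8)].
- True difference 20, dropout 25%/5%: 40·[1 − 0.25·(1 − w/8)] − 20·[1 − 0.05·(1 − w/8)] = 20 − 9·(1 − w/8).
- No true difference, dropout 25%/5%: 30·(0.05 − 0.25)·(1 − w/8) = −6·(1 − w/8).

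| Last visit | True 20, 15%/15% | True 20, 25%/5% | True 0, 25%/5% |
|---|---|---|---|
| Baseline | 17.0 | 11.0 | −6.0 |
| Week 2 | 17.75 | 13.25 | −4.5 |
| Week 4 | 18.5 | 15.5 | −3.0 |
| Week 6 | 19.25 | 17.75 | −1.5 |

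**Other direction.** With 5% herbal and 25% placebo, the true 20 points become 20 + 3·(1 − w/8), that is 23.0 (baseline) to 20.75 (week 6). The null case gives +6.0 to +1.5. The sign follows the arm that loses more women.

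**When there is no bias.** With no true effect and the same dropout rate and timing in both arms, the two arm means are equal and the contrast is 0.

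**The case against.** Much of the case for the plan stands. The direction and size of any bias cannot be read from the document: trajectories and the 25%/5% split are assumptions, and the plan gives only an overall 15%. Only the gastrointestinal criterion is tied to taking the drug. The others, including rash, flare or itching, need not differ by arm. With equal dropout the loss in the illustration is 0.75 to 3.0 of 20 points, which works against the herbal arm.

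Two stronger readings are tempting and are not supported.

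- A reader might infer that the primary standard error is too small because filled-in values count as real. The primary test uses one value per woman, independent between women, so the t-test standard error is valid for the quantity that carrying forward estimates. The trouble is that this is the wrong quantity. Understated uncertainty is arguable only for repeated-measures ANOVA on filled-in data, and no figure is available for that.
- A reader might infer that carrying forward is what mixes menstrual phases, since the Background says "Up to 78% of women with acne have premenstrual flares". In a 28-day cycle, week-2 and week-6 counts are indeed 14 days out of phase with week 8, but baseline and week-4 counts are in phase. In 23- or 33-day cycles, which the inclusion criteria admit, even an observed week-8 count is 10 days from the baseline phase (56 − 2 × 23 = 10; 2 × 33 − 56 = 10). The mismatch comes mainly from visit timing, and a mixed model without a phase term would not remove it.

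A separate analysis plan may add sensitivity analyses. That does not answer the point, because the article itself fixes the method for the main analysis.

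**Conclusion.** The concern holds in this limited form: the main analysis rests on a single missing-data method whose assumption conflicts with the expected course of the outcome, and no other stated analysis tests it. It should be changed.

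That the method is named, is the only one and governs the main analysis is certain from the text. That it can bias the contrast follows from the design. The size is illustrative: a true 20-point difference becomes 17.0 to 19.25 under the planned dropout split equally, and 11.0 to 17.75 under 25% vs 5%. A spurious 1.5 to 6.0 points arises under that split when there is no effect. These ranges rest on linear improvement and on dropouts resembling the rest of their arm. The document does not support saying that the result will be biased, or that it will favour the herbal arm.

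**What to change.** Replace last observation carried forward as the main method. Analyse percentage change in total lesion count at weeks 2, 4, 6 and 8 with a mixed model for repeated measures, with terms for treatment by visit, baseline count by visit, pattern (excess or deficiency) and centre. Make the week-8 treatment contrast primary. If log counts are preferred, state how zero counts are handled and that the effect is then a ratio, not a difference in mean percentage change.

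For the secondary repeated measures, use the same type of model in place of repeated-measures ANOVA or ANCOVA, at each scale's own visits. The menstrual-pain numeric rating scale, for example, is scheduled at weeks 0, 4, 8, 12 and 16, not at weeks 2 and 6.

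The mixed model assumes that dropout depends only on observed data, so add one sensitivity analysis for informative dropout. Keep last observation carried forward at most as a supportive analysis.

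The cost is a protocol modification, to be communicated as the Data management section requires for important changes, and slightly more analysis work. No new data are needed, because the counts are already scheduled, and the sample size does not change.
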